## Abstract

**Background:**

Spaghetti-wrist injuries representing Zone-5 flexor tendon lacerations remain a major challenge for hand surgeons despite the use of careful and meticulous surgical techniques and appropriate rehabilitation programs. Injuries in these regions can lead to adhesion formation, stiffness, and loss of hand function in view of its delicate and complex anatomy. One of the methods to prevent adhesion is the use of active flexion rehabilitation protocols. Its benefits have been shown in numerous reports on zone-2 injuries. However, there is a paucity of reports for this regime in Zone-5 and Spaghetti-wrist injuries.

**Methods:**

This study proposes a double-blind, single-center, randomized controlled trial (RCT) to compare the functional results of two rehabilitation methods following the repair of Spaghetti-wrist injuries. This includes the passive or active flexion therapy regime performed over six weeks. After fulfilling the inclusion criteria, adults aged 18–60 who have presented with spaghetti-wrist injuries will be selected. Patients will receive a comprehensive document outlining the study’s purpose, methodology, and follow-up schedule, which will be a part of the informed consent. 44 patients will be immobilized in a plaster slab and assigned equally to the passive or active flexion group. They will be assessed for primary and secondary outcomes, which include Tang’s criteria, independent digital function, sensory assessment, pinch and grip strength, and Michigan Hand Outcome Questionnaire (MCHQ), each at six and 12 weeks, six and 12 months. The study will follow the SPIRIT guidelines.

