Tang and colleagues have argued against starting early mobilization in the first few days, given the increased risk of the inflammatory response, which may exaggerate patients’ pain [5]. According to them and other authors, adhesions usually are not observed before the 10th day, and waiting for at least five days is recommended until the inflammatory phase is over [5–9]. However, the repaired tendons lose tensile strength significantly by two weeks and the excursion [5–7]. Therefore, it is recommended that mobilization be started from the fifth postoperative day onwards [5–9]. Mobilization decreases inflammation and helps reduce the work of flexion and friction [5–7]. As surgical methods and repair strength have increased, place and hold activities, synergistic wrist gliding exercises, and active gliding exercises have all been included in rehabilitation regimens [10]. These include immobilization regimens, place-and-hold exercises, and passive and active motion regimens [2, 3, 10]. Subsequently, many authors started studies on early active-motion protocols. As the evidence became clearer with improved functional results following early mobilization protocols, perhaps due to more efficient tendon gliding with minimized adhesions, the role of prolonged immobilization decreased. Later studies showed that tendons can heal without adhesion. In the only randomized study described for zone-5 injuries, Udayaraj et al. compared the Kleinert’s with a passive motion regime and observed the former to show better clinical improvement [11]. However, active flexion was not tested in these regimes, and the assessment duration was three months; hence, nerve injury and long-term assessment information were unavailable.

The main concern with active-motion programs is the risk of tendon rupture. However, the clarity on outcomes in the literature is lacking in view of variables like type and level of injury, technique of repair, and rehabilitation regimes [2, 8, 9, 12, 13]. Studies have also reported problems with passive mobilization protocols such as adhesions, joint contractures, and extensor lag [14]. For zone-5 flexor tendon injuries, no studies have compared the benefits of passive mobilization with early active motion therapy. In this regard, we propose conducting a randomized control trial (RCT) with the aim of comparing the functional results and complications of early active motion therapy versus passive mobilization for zone-5 flexor tendon injuries.

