### Randomization and blinding

Forty-four patients who fulfill the study’s inclusion criteria and have signed the informed consent form will be randomly assigned in a 1:1 ratio of 22 each, using block randomization for either the early active motion group or the passive motion group. This block randomization will be created using a computer-generated randomized controlled table. Randomization will be done 24 h before the surgery. An opaque sealed envelope with sequential numbers will hold the allocation sequence. The sole information on this envelope’s label will be its unique ID number, which is numbered progressively and includes study details. To ensure a blind and identical appearance at the time before surgery, an independent resident not involved in the treatment will receive the envelope. They will then prepare the patient for an active or passive flexion mobilization program (Table 1). The active versus passive mobilization protocol is tabulated in Table 1. The surgeons, hand therapists, and data assessors tracking the patients are thus blinded by this approach, which will be maintained until the end of the trial period.

**Table 1 Tab1:** Table showing the regime followed for the early active and the passive mobilization groups

Weeks	Early protected active	Passive mobilization
5th day	Dorsal thermoplastic splint with wrist 10^0^ flexion, MCP 40^0^ flexion, and IP full extension (Wrist immobilized till 6 weeks)	Dorsal thermoplastic splint with wrist 10^0^ flexion, MCP 40^0^ flexion, and IP full extension. (Wrist immobilized till 6 weeks)
Day 5–12	25% excursion (active flexion) of the affected digits at IP and MP joints (Remove the Velcro strap at the digital and palmar level) The patient is instructed to flex only 25% of the range possible and extend the fingers until full extension at IP joints within the splint. (20 repetitions/10 times a day of active flexion and extension exercise per hour)	Full passive flexion of the affected digits at IP and MP joints (Remove Velcro strap at digital and palmar level) The patient is instructed to flex the finger passively with the other hand. Fingers actively extended within the splint as far as possible. (20 repetitions/10 times a day of passive flexion and active extension exercise per hour)

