Day 12–21	50% excursion (active flexion) of the affected digits at IP and MP joints. (Remove the Velcro strap at the digital and palmar levels) The patient is instructed to flex only 50% of the range possible and extend the fingers until full extension at IP joints within the splint. (40 repetitions/ a day of active flexion and extension exercise) Ultrasound scar massage Tendon mobilization/gliding exercise and full ROM exercise started at 3 weeks.	Full passive flexion of the affected digits at IP and MP joints (Remove the Velcro strap at the digital and palmar levels) Flex the finger passively with the other hand. Fingers actively extended within the splint as far as possible. (40 repetitions/ a day of passive flexion and active extension exercise) Ultrasound scar massage Tendon mobilization/gliding exercise and whole ROM exercise started at 3 weeks.
Week 3–5	Splint modification - wrist brought to the neutral position. Remove the splint hol, d the wrist in neutral with the other hand, and encourage full active motion flexion and extension of IP and MP joints. Reapply the splint after exercise therapy. For the passive mobilization group, passive full flexion and active hold are started, followed by full active movement of flexion and extension as the weeks progress. (20 repetitions/ 10 times a day of active flexion and extension exercise per hour) At the end of the fourth week, full active motion range should be the goal (full extension at IP and MP joints) Low-intensity ultrasound scar massage (with intensities of 1 MHz, pulsed, 0.5 W cm-2) will be applied. Electrical stimulation of muscles in the hand for neurotmesis of the ulnar or median nerve (hypothenar/ thenar/ dorsal side for interossei) will be performed. Current type - Galvanic current () / Pulsed alternating current (AC) after re-innervation Pulse/cycle duration - >100 ms (GC) or 0.1-1 ms (Faradic current) Amplitude– as tolerated by the patient or till visible contraction observed Duration − 3 cycles of 30-30-30 contractions (Galvanic current), < 30 s (AC) Session frequency − 3–5 times/week, for 8–12 weeks approximately [16]	
Week 6	Wrist mobilization and electrical stimulation of long flexors, thenar, and hypothenar are started. Progression to full range of movements of wrist and fingers	

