Week 8	Blocking and light resistance exercises, full resistance is prohibited, splint is removed and worn only at night. Activities of daily living (ADL) are not yet advised. Introduction of the static splinting program to get at the interphalangeal joint (IP) extension in cases of flexor stiffness and flexion strapping program for extensor stiffness at IP joints Splinting for nerve injury will be added, which includes a knuckle bender splint if ulnar nerve injury is present and a first web spacer splint to keep the thumb in palmar abduction and extension at the CMC joint in median nerve injury	
Week 10	Stretch board exercises for IP and metacarpophalangeal (MP) joint stiffness and aggressive resistive mobilization started.	
Week 12	Desensitization exercises and activities of daily living started	

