### Follow-up

Patients in both groups will be followed up each at six weeks, three, six, and 12 months.

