### Outcomes

Primary outcome and Secondary outcomes.

Patient-related variables:

Age.Gender.Co-morbidities.Personal habits.Preoperative mobility.Patient injury data will be sub-grouped based on the classification of Koshy et al. They will be divided into three grades based on the lacerated structures, laceration type, and repair type [3].

Primary outcome: Tang’s criteria (Total active movement) [17].

Secondary outcome:

Independent FDS function.Sensory assessment.Pinch strength.Grip strength.MCHQ (Michigan Hand Outcome Questionnaire) [18]– Functional outcome.To look for causes of motor passivity that could influence the outcome, we propose using the Kinesiophobia Causes Scale (KCS). It is observed that fear of movement, considered to be a part of an individual’s personality, could be a major limitation to motor activity. This type of behavior is described as kinesiophobia and can be documented using this scale [19].

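### Grip and pinch strength are scheduled at six weeks, two weeks before Table 1 first allows light resistance; both tests should start at the 12-week visit

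*Protocol article*

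**What the plan says.** **Assessment schedule.** The abstract (Methods) lists the outcomes, among them "pinch and grip strength, and Michigan Hand Outcome Questionnaire (MCHQ), each at six and 12 weeks, six and 12 months". In the body, the Follow-up section says "Patients in both groups will be followed up each at six weeks, three, six, and 12 months", and the Outcomes section includes "Sensory assessment.Pinch strength.Grip strength" among the secondary outcomes. Neither section gives the strength tests a later start.

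**Loading limits (Table 1, under Randomization and blinding).**
- Day 5, both arms: splint with "IP full extension (Wrist immobilized till 6 weeks".
- Weeks 3-5: the splint comes off for exercise, to "encourage full active motion flexion and extension of IP and MP joints", and is then reapplied.
- Week 6: wrist movement and electrical stimulation begin, with progress towards full range. No resistance is listed.
- Week 8: "Blocking and light resistance exercises, full resistance is prohibited, splint is removed and worn only at night". Daily activities are still withheld.
- Week 10: stretch-board work for "joint stiffness and aggressive resistive mobilization started".
- Week 12: daily activities begin.

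**Stated hazard.** The Introduction says: "The main concern with active-motion programs is the risk of tendon rupture".

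**The concern.** Two parts of the protocol do not fit together. The assessment schedule calls for a strength test at week 6, while the rehabilitation schedule withholds all resistance until week 8 and full resistance beyond that. A strength test loads the repaired flexors whether it is labelled therapy or assessment.

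The assessor at the six-week visit has two choices, and neither is good:
- **Ask for full effort.** The repair is then loaded beyond what the trial allows in therapy, when rupture is the hazard the protocol itself puts first. A rupture during the test would count among the complications the trial sets out to compare, would be hard to separate from the effect of the regimen, and would disturb that patient's later range-of-motion values, which are the primary outcome.
- **Hold the patient back.** The recorded value then reflects the restriction, not the strength of the hand. The protocol defines no submaximal test, so assessors may also differ in how far they hold patients back.

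**Working it through.** **1. Timing**, from the abstract and Table 1:

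| Event | Week | Gap from the six-week test |
|---|---|---|
| First strength test | 6 | - |
| First light resistance, full resistance still barred | 8 | 8 - 6 = 2 weeks |
| Vigorous resistive work | 10 | 10 - 6 = 4 weeks |
| Second strength test, daily activities begin | 12 | 12 - 6 = 6 weeks |

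The 12-week visit falls 12 - 10 = 2 weeks after vigorous resistive work begins. It is the first scheduled visit after any resistance is allowed.

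**2. Tests affected.** Planned: 44 patients x 2 tests x 4 visits = 352. At six weeks: 44 x 2 = 88, or 88/352 = 25%. The remaining three visits hold 264. These are upper limits, since they assume no dropout.

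**3. Sample size, reproduced first.** Inputs from Sample size calculations: effect size f = 0.3, two-sided 5% level, 80% power, m = 4 time points, correlation 0.3. For the between-group test in a repeated-measures ANOVA, the noncentrality is N f² m / [1 + (m - 1)ρ], with 1 and N - 2 degrees of freedom. At N = 44 it is 44 x 0.09 x 4 / 1.9 = 8.34, and power is 0.805. The smallest even N reaching 0.80 is 44, which agrees with the protocol. This sizing rests on the primary outcome, so it does not change if strength loses a visit.

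**4. Precision lost for strength.** With equal variances and a common correlation r, the variance of a mean over k visits is proportional to [1 + (k - 1)r]/k.

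| r | k = 4 | k = 3 | SE ratio, √(k = 3 / k = 4) |
|---|---|---|---|
| 0.3 | 1.9/4 = 0.475 | 1.6/3 = 0.533 | 1.060 |
| 0.5 | 2.5/4 = 0.625 | 2.0/3 = 0.667 | 1.033 |
| 0.7 | 3.1/4 = 0.775 | 2.4/3 = 0.800 | 1.016 |

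The correlation of 0.3 is the protocol's figure for the primary outcome, borrowed here for strength. The other two values show the range.

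**5. The same cost as power.** If strength had f = 0.3 and correlation 0.3, three visits would give a noncentrality of 44 x 0.09 x 3 / 1.6 = 7.43 and power of about 0.76, against 0.81 with four visits. The protocol claims no power for strength.

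**The case against.** The strongest case on the other side has four parts.

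**The schedule rests on one sentence.** Only the abstract ties strength to six weeks. The body lists visits and outcomes separately, and Figure 1, which could not be consulted here, may say more. This is a fair caution. Still, the abstract's wording covers each listed outcome, and nothing in the available text contradicts it.

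**Table 1 governs exercises, and the effort is not described.** Both statements are true. A submaximal or surgeon-cleared test at six weeks would not contradict anything written, and a line specifying one would keep the visit. But no such limit is stated, and a deliberately submaximal value does not measure strength. That remedy would address safety and leave an outcome that is hard to interpret.

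**The plan already makes the repaired units contract at week 6.** The week 6 row starts electrical stimulation of the long flexors and progress towards full range. That shows contraction is accepted. It does not permit forceful gripping, and the week 8 row still bars full resistance.

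**Six weeks is the visit nearest the treatment contrast.** The regimens differ early, and both arms share one programme from week 6. If a strength difference is largest then, dropping the visit loses signal as well as precision, and the standard-error figures above do not count that. This part stands as a real cost. It is tolerable because strength is a secondary outcome and range of motion, the questionnaire and the other assessments remain at six weeks.

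**Conclusion.** The concern holds. The six-week grip and pinch tests are out of step with the trial's own loading limits, by 2 weeks for light resistance and 4 weeks for vigorous resistive work, and up to 25% of planned strength measurements are affected.

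This rests on one assumption that the article does not spell out: that grip and pinch testing is a forceful resisted effort, as it ordinarily is. The visit-by-outcome schedule is taken from the abstract.

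The limits of the point are clear. Both arms share the same visits and the same programme from week 6, so no directional bias is shown. The document gives no basis for putting a number on the rupture risk. The primary outcome and its sample size are not in question. The change should be made because the risk is avoidable and the six-week value is hard to interpret under either way of running the test. Confidence is medium.

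**What to change.** Amend the assessment schedule so that grip and pinch strength are first measured at 12 weeks and again at 6 and 12 months. State that the repeated-measures analysis of these two outcomes uses three time points. Keep all other six-week assessments as planned, including the Michigan questionnaire.

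The cost is a short amendment and the loss of one visit in four for two secondary outcomes. That includes any early difference in strength that might have shown at six weeks, and the modest loss of precision and power set out above. No extra visits or patients are needed.

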**Discussion:**

The proposed RCT compares early active and passive flexion regimes’ functional results in zone-5 flexor tendon injuries. This trial is unique as an active flexion regime was not described earlier in a major comparison study. It will answer the role and possible benefits of a more aggressive early active flexion program. Additionally, the study will give information on patient-reported outcomes and address the incidence of complications in a much longer follow-up of one year.

**Trial registration details:**

The institute ethics committee approval was confirmed for the study (approval No. IEC – 383/2022), and registration for the Clinical Trial Registry of India was completed (CTRI/2023/03/050721).

## Introduction

Zone-5 flexor tendon injuries remain a major challenge for hand surgeons despite using a careful surgical technique and appropriate rehabilitation programs. This is mainly due to adhesions, joint stiffness, persisting nerve injury, and subsequent loss of hand function [1, 2].

There is considerable controversy on the issue of whether to mobilize the tendon early or late after repair. While some advocate for starting physical therapy as soon as possible after tendon repair, others favor longer periods of rest [3, 4]. Zone-5 injuries present challenging problems for surgeons and hand therapists due to their unique and complicated anatomy. Multiple tendons add to the burden of strong adhesions and possible loss of independent motion. Nerve injury repair will be at risk, particularly the median nerve, as it requires fine, meticulous sutures, which need protection and maintenance of low tension with wrist flexion. There is a theoretical risk of disruption of the nerve repair following early mobilization of bunched-up tendon repairs in a tight and edematous compartment. A similar risk exists for arterial repair, particularly the ulnar artery, which is very close to the flexor tendons. However, strict immobilization may also lead to robust adhesions, which may stress the tendon and nerve repair after delayed therapy [4].

Tang and colleagues have argued against starting early mobilization in the first few days, given the increased risk of the inflammatory response, which may exaggerate patients’ pain [5]. According to them and other authors, adhesions usually are not observed before the 10th day, and waiting for at least five days is recommended until the inflammatory phase is over [5–9]. However, the repaired tendons lose tensile strength significantly by two weeks and the excursion [5–7]. Therefore, it is recommended that mobilization be started from the fifth postoperative day onwards [5–9]. Mobilization decreases inflammation and helps reduce the work of flexion and friction [5–7]. As surgical methods and repair strength have increased, place and hold activities, synergistic wrist gliding exercises, and active gliding exercises have all been included in rehabilitation regimens [10]. These include immobilization regimens, place-and-hold exercises, and passive and active motion regimens [2, 3, 10]. Subsequently, many authors started studies on early active-motion protocols. As the evidence became clearer with improved functional results following early mobilization protocols, perhaps due to more efficient tendon gliding with minimized adhesions, the role of prolonged immobilization decreased. Later studies showed that tendons can heal without adhesion. In the only randomized study described for zone-5 injuries, Udayaraj et al. compared the Kleinert’s with a passive motion regime and observed the former to show better clinical improvement [11]. However, active flexion was not tested in these regimes, and the assessment duration was three months; hence, nerve injury and long-term assessment information were unavailable.

The main concern with active-motion programs is the risk of tendon rupture. However, the clarity on outcomes in the literature is lacking in view of variables like type and level of injury, technique of repair, and rehabilitation regimes [2, 8, 9, 12, 13]. Studies have also reported problems with passive mobilization protocols such as adhesions, joint contractures, and extensor lag [14]. For zone-5 flexor tendon injuries, no studies have compared the benefits of passive mobilization with early active motion therapy. In this regard, we propose conducting a randomized control trial (RCT) with the aim of comparing the functional results and complications of early active motion therapy versus passive mobilization for zone-5 flexor tendon injuries.

## Methods and analysis

### Study design

The double-blind RCT will be conducted at a single tertiary referral center, comparing the functional results and complications after using two different rehabilitation programs in patients presenting to the Trauma Centre and Outpatient Department of Hand Surgery with zone-5 flexor tendon injuries. The timeline for the trial procedure is demonstrated in Fig. 1. Patients presenting from March 2023 to February 2026 fulfilling the inclusion criteria will be explained about the procedure, the risks and advantages involved, the type of subsequent rehabilitation, and evaluation by the trained instructors. All the patients will be required to provide written informed consent, and the data collected will be documented and stored for the study. The enrollment evaluation checklist and the informed consent obtained are provided in supplementary files 1 and 2 each. The protocol is prepared as recommended in the guidelines laid out in the Standard Protocol Items: Recommendations for the Intervention Trials (SPIRIT) [15].

